### Interventions

Participants are provided with an iPad (5th generation, wifi) with all the apps needed for the training installed and a mail to contact the study coordinator (who is the only one aware of group allocation) if they have problems. The display of apps and contents in the iPads are remotedly controlled by Zuludesk (now Jamf SCHOOL; https://www.jamfschool.com/). Participants are also provided with a Fitbit Flex 2 (https://www.fitbit.com/flex2) to monitor physical activity and sleep patterns during the weeks of training. Figure 3 shows the materials given to the participants to undergo the training period: an iPad (5th generation) enrolled in the study with all the apps installed and a Fitbit Flex 2.

**Figure 3 F3:**
[figure not shown]
Materials provided to participants to follow the home-based training.

The coordinator of the study follows the adherence to the training on a daily basis, as well as ensures that participants send and synchronize the required information (pictures of the food intake and Fitbit synchronization). The intervention is threefold (see details in Figure 1).

#### Cognitive Training

All participants undergo a 6-week period of home-based executive function training, five sessions per week, with a duration of 30–45 min per session.

The *executive functions training* consists of working memory training by the Cogmed software (http://www.cogmed.com) and executive functions training (mainly inhibitory function, decision-making, and cognitive flexibility training) by Cognifit software (https://www.cognifit.com), both with adaptive difficulty. These apps are installed in the iPads provided to participants.

The *control task training* will consist of the same training by Cognifit software with non-adaptive difficulty, minimizing the executive component and without increasing difficulty. A control task training for Cogmed was not used because the platform does not provide it anymore.

Participants are asked to perform the training from Monday to Friday. If they cannot perform one or two sessions during the week, they are allowed to make up these sessions during the weekend. In the case of an occasional unfulfillment of the training, we offer the participants to rest 1 week more in training, so they can finish it satisfactorily. In any case, we will extend the training more than 1 week. In the baseline visit with the participants and families, we will also register the number of hours per day/week subjects use to play to other videogames to control for concomitant interventions.

The rest of the procedure will be the same for both groups.

#### Psychoeducation and Food Registry

During the 6 weeks of training, participants are required to send daily pictures of the food intakes to evaluate if the training exerts a change in the eating patterns. We will consider a weekly register as complete, when we have at least 4 days in a week complete, from which one should be a weekend day.

In addition, participants receive dietary and healthy lifestyle counseling by means of animated presentations displayed on Prezi (www.prezi.com). The purpose of those presentations are to encourage participants and their families to learn basic healthy habits by sending them daily presentations with a variety of contents that include healthy food recommendations, funny recipes, enhancing physical activity, and strategies to manage emotion and behavior. Table 2 show the contents of the 30 psychoeducational sessions. Figure 4 shows an example of a Prezi presentation.

**Table 2 T2:** Prezi contents.

	**Prezi contents**
Session 1	Characteristics of a healthy diet (Mediterranean diet)
Session 2	Family activities: help your children to develop healthy habits, “you are a team”
Session 3	Funny colorful recipes
Session 4	Changing your feeding habits: diary goals
Session 5	Introducing new food by playing
Session 6	Buying with responsibility (I)
Session 7	Buying with responsibility (II)
Session 8	Do not snack between meals: just five meals a day!
Session 9	Funny tricks: new recipes
Session 10	Make it easier: weekly menu for planner
Session 11	Going out to a restaurant: some tricks to deal with it
Session 12	Avoid sedentary lifestyle: no more than 2 h with TV and computer
Session 13	Recipe: fish hamburger
Session 14	What do I do if I am nervous?: Strategies to manage your nervousness (I)
Session 15	Eat slow: it can be helpful to your health
Session 16	Physical exercise: a minimum of 60 min per day!
Session 17	Strategies to manage your nervousness (II)
Session 18	Recipe: carrot, zucchini, and York ham (or turkey) quiche
Session 19	Strategies to manage your nervousness (III)
Session 20	Mindful eating: to be conscious on what we eat and how to do it
Session 21	Strategies to manage your nervousness (IV)
Session 22	Recipe: fish meatballs
Session 23	Childhood obesity as a risk factor to develop health disorders
Session 24	Strategies to manage your sadness
Session 25	Recipe: peppers stuffed with potato omelet
Session 26	Funny activities to do on my free time: fighting boredom!
Session 27	Recipe: baked zucchini sticks
Session 28	Positive self-esteem and taking responsibilities!
Session 29	Recipe: zucchini and onion pancakes
Session 30	Last advices and good-bye!

**Figure 4 F4:**
[figure not shown]
Screenshots of a Prezi daily presentation.

#### Activity and Sleep Pattern Registry

Furthermore, to control for the effect that physical activity and sleep patterns may have on food decisions and BMI, we will register them over the training period by a Fitbit Flex 2. Participants can check their trackings on their iPads. When they do some progresses, Fitbit sends them badges and positive-feedback messages (https://blog.fitbit.com/fitbit-badges/). We consider a register as complete when it has at least 10 h of register/day at least 4 days/week (46).

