**Table d39e458:** 

**Data category**	**Information**
Primary registry and trial identifying number	ClinicalTrials.gov NCT03615274
Date of registration in primary registry	August 3, 2018
Secondary identifying numbers	2016-16-10
Source(s) of monetary or material support	Fundació La Marató de TV3
Primary sponsor	Fundació La Marató de TV3
Contact for public and scientific queries	PI: [name] [name] [contact] Coordinator: [name] [name] [contact] Department of Clinical Psychology and Psychobiology Institut de Neurociències University of Barcelona, Barcelona, Spain, 08035
Public title	Executive Function Training in Childhood Obesity: Food Choice, Quality of Life, and Brain Connectivity (TOuCH)
Scientific title	Executive Function Training in Childhood Obesity: Food Choice, Quality of Life, and Brain Connectivity (TOuCH)
Countries of recruitment	Spain
Health condition(s) or problem(s) studied	Childhood obesity
Intervention(s)	Experimental: experimental
	Active comparator: placebo non-adaptive training
Key inclusion and exclusion criteria	Ages eligible for study: 9–12 years Sexes eligible for study: all Accepts healthy volunteers: no
	Inclusion criteria: being obese according to the criteria by Cole et al. (28)
	Exclusion criteria: neurological, psychiatric, or developmental disorder
Study type	Interventional (clinical trial)
	Allocation: randomized intervention model. Parallel assignment masking: double blind (participant, family, investigator, and outcomes assessor)
	Primary purpose: treatment
Date of first enrollment	Estimated for February 2, 2018
Target sample size	30
Recruitment status	Recruiting
Primary outcome(s)	Change from baseline in cognitive, MRI, food choice, and BMI measures at the end of the intervention and follow-up at 12 months
Key secondary outcomes	Change from baseline in emotional state, physical activity, and quality-of-life measures at the end of the intervention and follow-up at 12 months

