### Outcomes

We will assess the effect of the intervention on BMI, food choice, global cognition, and neural plasticity. Secondary measures will be emotion/behavior, QoL, and physical activity (see details of the registered protocols in Table 1). There will be three evaluation timepoints: (1) *baseline assessment* (T0); (2) *post-training assessment* (T1), which will be performed after the 6-week training period; and (3) 1-year follow-up assessment (T2), which will be done 12 months after T0, with a leeway of 1 month.

We will collect cognitive, psychological (emotional and quality of life measures), and MRI data in all three time points. Participants' parents will also be interviewed in T0 and T2. Socio-economical data from family, school information, and habits of nutrition and physical exercise from children will be obtained to characterize the sample.

Food, activity, and sleep hours registries will be collected during the 6 weeks of training and for a week at 12-month follow-up.

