#### Anthropometric Measures

The pediatric assessment will consist of height, weight, waist circumference, blood pressure, puberal state, and personal and familial history. Height and weight will be converted into BMI.

BMI will be considered a primary measure.

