#### Food Choice Registry

During the training period and for 1 week at 12 months' follow-up, participants will send pictures of the daily intake of food and drinks. These will be collected in tables quantifying the type of food per day and week. We will also administer the Kidmed questionnaire (54) at T0, T1, and T2.

A change in food choice will also be considered a primary measure.

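### The protocol says it will control for activity and sleep recorded after randomisation when assessing food choice and BMI, and the analysis plan neither specifies nor rules out that adjustment

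*Protocol article*

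**What the plan says.** The section Activity and Sleep Pattern Registry gives the reason for the tracker: "to control for the effect that physical activity and sleep patterns may have on food decisions and BMI". The Outcomes section gives the timing: "Food, activity, and sleep hours registries will be collected during the 6 weeks of training and for a week at 12-month follow-up". No tracker period before training is described.

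Both targets of that control are primary. Anthropometric Measures says "BMI will be considered a primary measure", and Food Choice Registry says "A change in food choice will also be considered a primary measure".

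Physical activity is also an outcome. The Outcomes section says "Secondary measures will be emotion/behavior, QoL, and physical activity", and Table 1 lists among the key secondary outcomes "Change from baseline in emotional state, physical activity, and quality-of-life measures at the end of the intervention and follow-up at 12 months". Sleep appears in neither list.

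The Introduction names reduced physical activity among the behaviours that executive impairment seems to underlie.

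The Data Analysis Plan specifies a repeated-measures general linear model for BMI and cognition and linear mixed models for food choice. Neither names activity or sleep as a covariate. Multiple regression is allowed when confounders are not well controlled, and the confounders listed are age, sex, IQ, handedness, and socioeconomic and educational status.

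**The concern.** A variable measured after randomisation that the treatment may change is not a confounder of the treatment effect. It may lie on the path from treatment to outcome. Here the protocol gives physical activity two roles: something the training is tested for changing, and something to be held constant when the training's effect on BMI and food choice is judged.

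Read in its ordinary statistical sense, the stated purpose would have two consequences if carried out. Any benefit of training that comes about through more activity or better sleep would be taken out of the estimate. The comparison would also lose the protection of randomisation, because activity shares causes with diet and BMI (family motivation is an obvious candidate), and conditioning on activity makes the arms differ on those causes. Sleep has the same timing problem, although it is not a listed outcome.

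**Working it through.** No figure in the protocol is at stake and there is none to reproduce. The check sets the statements side by side and then illustrates the mechanism.

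**Side by side**

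1. *Timing.* The activity and sleep registries cover the six training weeks and one week at 12 months. All these values follow allocation, so none can serve as a baseline covariate.
2. *Role as a variable to control.* The registry section names food decisions and BMI as the outcomes to be protected from activity and sleep. Both are primary.
3. *Role as an outcome.* The Outcomes section and Table 1 both list physical activity as secondary.
4. *Plausibility of an effect.* The Introduction's link between executive impairment and low activity means that, on the protocol's own rationale, training could raise activity.
5. *Analysis plan.* It contains no activity or sleep term, and no statement that such terms are excluded. Its list of confounders contains no tracker variable. The registry section therefore either extends that list or conflicts with it, and the text does not say which.

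**Illustration (all inputs assumed; none comes from the protocol)**

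Let T be allocation (0 or 1), M activity, Y the outcome and U an unmeasured common cause with SD 1:

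- M = a·T + u·U + noise, with SD 1 within an arm
- Y = d·T + b·M + v·U + noise, where the part not due to T or M has SD 1

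Without M in the model, the coefficient of T is the total effect, d + a·b. With M in the model, it is d − a·u·v, because among children with the same activity the expected value of U differs between arms by −a·u.

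Take a total effect of 0.50 and a = 0.5.

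| Share through activity | b | d = 0.50 − a·b | Adjusted, u = v = 0 | Adjusted, u = v = 0.5 |
|---|---|---|---|---|
| 20% | 0.2 | 0.40 | 0.40 | 0.40 − 0.5 × 0.25 = 0.275 |
| 50% | 0.5 | 0.25 | 0.25 | 0.25 − 0.5 × 0.25 = 0.125 |

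A simulation of 400,000 records per scenario agrees. The adjusted estimates were 0.393 and 0.253 without the common cause, and 0.275 and 0.122 with it. The unadjusted estimate stayed between 0.495 and 0.503 in every scenario.

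Two limits follow from the same formula:

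- If training does not change activity (a = 0), the adjusted coefficient equals the total effect. The simulation gave 0.498 and 0.494.
- If the common cause acts on activity and outcome in opposite directions (v = −0.5), the bias term becomes +0.125 and the adjusted values are 0.525 and 0.375. The direction of the bias is therefore not fixed.

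**The case against.** The strongest reply is that the protocol does not plan this adjustment at all. The clause sits under Interventions and explains why data are collected. No model in the Data Analysis Plan contains activity or sleep, and covariate detail may be settled in a statistical analysis plan that is not shown. The phrase *control for* is also used loosely in this article. Cognitive Assessment applies it to IQ, which the analysis plan first handles as a baseline comparability check, and Cognitive Training applies it to videogame hours, with no model attached. The Abstract and Interventions describe the tracker as a monitoring device. Both arms receive the same tracker and feedback ("When they do some progresses, Fitbit sends them badges and positive-feedback messages"), so the device itself creates no difference between them.

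Much of this stands. A reader might infer that the plan conditions on a mediator in its primary models. The documents do not support that: they state an intent that no named model implements, and monitoring is a possible reading. The badges and messages, being common to both arms, are no evidence that training shifts activity.

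The reply does not dispose of the point. The purpose is written down and names two primary outcomes. Its plain statistical meaning is adjustment, and nothing elsewhere withdraws it. The other uses of the phrase concern IQ and videogame hours taken at baseline, where adjustment would be harmless. An identical tracker in both arms balances the device but does not prevent executive training from changing activity. The point rests on what the text states and on its conflict with the text's own outcome list, not on missing detail.

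**Conclusion.** The point holds as a conflict between a stated purpose and the outcome list, left unresolved by the analysis plan. If the purpose were carried out as adjustment, the estimate for BMI or food choice would no longer be the total effect of allocation and could be biased by common causes.

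The size cannot be derived from the documents. It depends on whether training changes activity or sleep, how far these affect the outcome, and how strong the shared causes are. The illustrative fall from 0.50 to between 0.40 and about 0.12 shows the mechanism and is not a forecast.

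Two further inferences are tempting and unsupported:

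- That a definable part of the small BMI effect cited under Sample Size (0.20, from a trial with a passive control group) would be lost. Nothing in the protocol says how much of any effect passes through activity.
- That children without a complete tracker register would drop out of the analysis. No such rule is stated, and the section on missing data mentions both multiple imputation and list-wise deletion.

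The correction is worth making because it is cheap and protects the randomised comparison for two primary outcomes.

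**What to change.** 1. Add to the Data Analysis Plan that no activity or sleep value recorded after randomisation enters the primary models for BMI or food choice.
2. Reword the purpose in Activity and Sleep Pattern Registry so that the tracker data describe activity and sleep by arm, with activity analysed as the listed secondary outcome.
3. Restrict covariate adjustment to baseline variables. Exercise and nutrition habits qualify only if recorded at T0. The Outcomes section places the parent interviews at T0 and T2 but does not say when the habits are recorded, so this should be stated.
4. Label any model adjusted for activity or sleep as exploratory mediation, and state its assumption of no unmeasured common causes.

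The cost is a few sentences. No new data are needed, and the sample size does not change.

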### Outcomes

We will assess the effect of the intervention on BMI, food choice, global cognition, and neural plasticity. Secondary measures will be emotion/behavior, QoL, and physical activity (see details of the registered protocols in Table 1). There will be three evaluation timepoints: (1) *baseline assessment* (T0); (2) *post-training assessment* (T1), which will be performed after the 6-week training period; and (3) 1-year follow-up assessment (T2), which will be done 12 months after T0, with a leeway of 1 month.

We will collect cognitive, psychological (emotional and quality of life measures), and MRI data in all three time points. Participants' parents will also be interviewed in T0 and T2. Socio-economical data from family, school information, and habits of nutrition and physical exercise from children will be obtained to characterize the sample.

Food, activity, and sleep hours registries will be collected during the 6 weeks of training and for a week at 12-month follow-up.

#### Anthropometric Measures

The pediatric assessment will consist of height, weight, waist circumference, blood pressure, puberal state, and personal and familial history. Height and weight will be converted into BMI.

BMI will be considered a primary measure.

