This project has the purpose of evaluating the impact of executive functions training in BMI, food choice, and cognition in children with obesity as well as in their emotional state and QoL. These changes are expected to induce cerebral plasticity that will be measured by MRI connectivity. We hypothesize that children with obesity undergoing the cognitive training program will perform better than active controls in cognitive measures, take better food-related decisions, and consequently, show changes in brain connectivity, emotional state, and QoL measures at the end of the intervention and during the follow-up at 12 months. We also expect them to maintain BMI.

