### Data Analysis Plan

#### Demographic, Neuropsychological, and QoL Variables

For demographic variables, we will use a descriptive analysis of the variables and a comparative analysis between the training and control groups at baseline. We will use the χ^2^ test (and if this is not applicable, Fisher's exact) for categorical variables and Student's *t*-test (if not applicable, the Mann–Whitney *U*-test) for quantitative variables to check that randomization has successfully distributed the possible confounding variables (age, sex, IQ, manual dominance, socioeconomic, and educational status).

For the evaluation of the effectiveness of treatment on BMI and cognition, we will perform a general linear model for repeated measures analysis including these two variables as primary outcomes. We will perform further *post-hoc* analysis evaluating the effects on cognitive domains and emotional and QoL measures if appropriate. Means comparisons will be performed by Student's *t*-test, if the conditions of application are met and confounding variables have been well-controlled (otherwise, adjusted analyses will be performed by multiple regression). Multiple comparisons will be tested by Bonferroni correction. Effect size will also be calculated according to Hunter and Schmidt (58). All statistical tests will be carried using a two-sided test with the significance level set at 5% with the software Statistical Package for the Social Sciences (SPSS, version 24.0) or R (version 3.6.3).

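### The BMI primary is not standardised for age and sex in growing children, and its only hypothesis, that BMI is maintained, has no comparator or margin

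*Protocol article*

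**What the plan says.** Under Anthropometric Measures the protocol article states "Height and weight will be converted into BMI" and then "BMI will be considered a primary measure". Study Sample and Setting repeats the conversion. Neither section names a standard-deviation score, a percentile or a percentage of a cut-off. Eligibility, by contrast, rests on a published definition of obesity in children (Table 1: "Inclusion criteria: being obese according to the criteria").

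The last paragraph of the Introduction gives the aim as "evaluating the impact of executive functions training in BMI, food choice, and cognition in children with obesity". For cognition it sets a comparator: trained children "will perform better than active controls in cognitive measures". BMI gets a separate sentence: "We also expect them to maintain BMI". It does not say whether this is relative to baseline or to the control group, and it gives no margin.

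Table 1 registers the primary outcome as "Change from baseline in cognitive, MRI, food choice, and BMI measures at the end of the intervention and follow-up at 12 months". For BMI and cognition, the Data Analysis Plan states "we will perform a general linear model for repeated measures analysis including these two variables as primary outcomes", with all tests two-sided at 5%.

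**The concern.** BMI changes with growth between 9 and 13 years, and the change depends on age, sex and pubertal stage. Over 12 months an unchanged plain BMI can therefore be a fall relative to a child's peers, and a modest rise can be ordinary growth. A statement about one arm's change in plain BMI cannot separate these from an effect of training.

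The hypothesis adds to this. Maintenance, read as no change from baseline in the trained children, is a claim of no difference. A two-sided difference test can reject no difference but cannot establish it. In a small trial a non-significant result is likely even when BMI has moved, and a plan that expects maintenance without defining it leaves room for that result to be reported as success.

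**Working it through.** **Inputs from the protocol article.** 15 completers per arm (Sample Size); two-sided 5% (Data Analysis Plan); randomisation stratified by sex, age and manual dominance (Study Design); T2 at 12 months after T0, give or take one month (Outcomes); losses of six of 22 in the experimental arm and two of 17 in the control arm (Details of the Sample Enrollment to Date). No SD of BMI change, growth rate or margin is given, so results are in SD units of change unless marked as assumed. The sample size is justified by studies of similar size, not by a calculation, so there is no figure of the plan's own to reproduce.

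**1. Precision of the between-group contrast.** Half-width of the 95% CI = t(28, 0.975) × √(2/15) = 2.048 × 0.365 = 0.75 SD. This follows from 15 per arm and is the same in SD units for any BMI metric.

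**2. Maintenance read as no change within the trained arm (n = 15).** Half-width = t(14, 0.975)/√15 = 2.145/3.873 = 0.55 SD. The probability of a non-significant two-sided test is:

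| True rise (SD of change) | P(non-significant) |
|---|---|
| 0.2 | 0.89 |
| 0.3 | 0.81 |
| 0.5 | 0.56 |

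If no true change is assumed, the smallest rise that 15 children can exclude with 80% power and a one-sided 2.5% bound is (1.960 + 0.842)/√15 = 0.72 SD.

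**3. Maintenance read as not worse than control.** The smallest margin at 15 per arm is (1.960 + 0.842) × √(2/15) = 1.02 SD. A margin of 0.5 SD would need 63 per arm.

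**4. Maintenance read as a smaller rise than control.** The two-sided test is then the right kind of test. At 15 per arm it has 80% power only for d of about 1.02. For d = 0.20, the BMI effect that Sample Size cites from working-memory training in children with obesity, power is about 0.08.

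**5. Does growth bias the randomised contrast?** This was simulated with 20,000 runs per setting, two arms of 15, and an assumed residual SD of 12-month change of 1.2 kg/m². Assumed growth was 0, 0.5 or 1.0 kg/m² per year, either constant or varying by 0.15 kg/m² per year of age, with the one-month visit leeway.

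- With no treatment effect, the between-group test rejected in 4.9% to 5.3% of runs and the mean difference was about 0. Growth does not bias the contrast.
- The mean within-arm change absorbed the growth in full (+0.5 or +1.0 kg/m²). At 0.5 kg/m² of growth and no treatment effect, the trained arm's own test was still non-significant in 67% to 69% of runs, so an ineffective programme would often look like maintenance.
- Age-dependent growth raised the SD of change only from 1.20 to √(1.2² + 0.15² × 16/12) = 1.21, about 1%. Variation from sex and puberty was not simulated.

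**6. Exposure to imbalance.** Losses are 6/22 = 27% against 2/17 = 12%, and the target counts completers only. Pubertal state is recorded but is not among the confounders that the Data Analysis Plan lists for the baseline check.

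**The case against.** The strongest reply is that the planned comparison is randomised, concurrent and stratified by sex and age, so expected growth cancels. That stands. A reader might infer that plain BMI confounds growth with the treatment effect. The documents do not support this for the between-group contrast, and the simulation shows none. What remains is some loss of precision, and exposure to chance imbalance or selective completion.

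A reader might also infer that the planned test cannot address the hypothesis at all. That holds only if maintenance means no change from baseline. The preceding sentence of the Introduction compares with active controls, so a smaller rise than in controls is a fair reading, and a difference test suits it. The protocol also nowhere says that a non-significant result will be taken as maintenance.

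An article may condense a fuller protocol, so silence on a standard-deviation score is weak evidence alone. The authors know the distinction: for one hospital-based multidisciplinary programme, Sample Size cites d = 1.75 for a standardised BMI and d = 0.66 for an adjusted one. But that also shows how far the choice of metric can move the result, and the outcome section, read plainly, names BMI and nothing more.

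Finally, growth matters little at T1. Under the assumed 0.5 to 1.0 kg/m² per year, six weeks adds 0.06 to 0.12 kg/m² (× 6/52). The point bears mainly on T2.

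**Conclusion.** The point holds as a weakness in metric and hypothesis, not as a bias in the trial. The BMI primary is unstandardised in children who will grow for a year, and the one stated expectation does not say what BMI is maintained against or within what margin. The between-group test remains valid. Any within-arm reading of maintenance does not, and a null result at 15 per arm leaves differences of about 0.75 SD of change either side of the estimate open. That width comes from the sample size, and standardising BMI will not narrow it in SD units. The gain from standardising is mainly in interpretation and in protection against imbalance; the gain in precision may be small. The SD-unit results rest only on 15 per arm, the 5% level and approximate normality. The growth rates and the SD of 1.2 kg/m² are assumptions.

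**What to change.** - Make the primary BMI measure age- and sex-standardised, from a named reference: for example, BMI as a percentage of the age- and sex-specific obesity cut-off, or a standard-deviation score. Whether the eligibility reference supplies both cannot be checked from the article, so the reference must be named. Keep plain BMI as a descriptive or sensitivity measure.
- State the BMI hypothesis as a between-group difference in that measure at T1 and at T2, adjusted for its T0 value and reported with the 95% CI.
- State that a non-significant result will not be read as BMI maintained.

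Record the change before any between-group analysis of BMI, so that the metric is not chosen on the results. The cost is a recalculation from height, weight, sex and age at each visit, with no new data collection, and results that compare less directly with studies reporting plain BMI.
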